# 1. Aim of the study

The overall aim of the iGugu Study is to pilot the surveillance of reproductive tract infections (RTIs) among young men and woman aged 15 to 24 years old in the Africa Centre DSA using a 14-week round of the Africa Centre individual surveillance platform as a sampling frame.

# 2. Study design

The study design is cross-sectional of young men and women

# 3. Study population

Young men and women aged 15-24 years living in the Africa Centre DSA

Eligibility criteria for enrollment:

- participants aged 15-24 years at the time of sampling
- resident at the time of the study
- willing to participate and able to provide informed consent

# 4. Sample size

447 young men and women agreed to participate and provided informed consent. Details on sampling methods and intended sample size are provided in the excerpt of the study protocol (Version 1.3, 09 Sept 2016) below:

# 5. Study objectives

## 5.1 Primary objectives

1. Investigate the acceptability and feasibility of population-based sampling of RTI through the individual surveillance platform at the Africa Centre DSA.
2. Estimate the population prevalence of curable STIs (i.e. Chlamydia trachomatis, Neisseria gonorrhoeae, Trichomonas vaginalis, syphilis), HSV-2, *vaginal yeast* and BV (young women only) in the Africa Centre DSA
3. Develop clinical pathways for the treatment of curable RTIs diagnosed through the RTI surveillance platform

## 5.2 Secondary objectives

1. Develop capacity for RTI/STI testing at the Africa Centre Laboratory
2. Store samples for future testing of HPV, vaginal microbiome, metagenomics and transcriptomics (young women only) and other determinants of physiological vulnerability when funding becomes available

# 6. Objectives for the analysis plan

The analysis plan covers two of the study primary objectives:

1. Investigate the acceptability and feasibility of population-based sampling of RTI through the individual surveillance platform at the Africa Centre DSA.
2. Estimate the population prevalence of curable sexually transmitted infections (i.e Chlamydia trachomatis, Neisseria gonorrhoeae, Trichomonas vaginalis, syphilis), HSV-2 and bacterial vaginosis (BV) in the Africa Centre DSA

And the third objective is to:

1. Investigate the risk factors for RTIs among young men and women aged 15-24 years in Africa Centre DSA

# 7. Study outcomes

## 7.1 Feasibility

Feasibility will be measured as the proportion of sampled individuals who were visited and contacted. Reasons for non-contact (e.g. migration) among sampled individuals will also be presented.

## 7.2 Acceptability

Acceptability of RTI sample collection and testing will be measured by the following outcomes:

- proportions of individuals contacted who agreed to participate
- proportions who agreed to each sample collection (e.g. blood, vaginal swabs and urine)
- median and interquartile range of responses to visual analogue scales (VAS) measuring acceptability of sample collection

Variables to be used are described in the next section (Section 1.7).

## 7.3 Prevalence of reproductive tract infections (RTIs)

The following RTIs will be measured:

- Chlamydia trachomatis (Presence/absence)
- Neisseria gonorrhoeae (Presence/absence)
- Trichomonas vaginalis (Presence/absence)
- Syphilis: negative (TP-/VDRL-); early or previously treated infection (TP+/VDRL-); active syphilis (TP+/VDRL+ low titer [<1:8]; TP+/VDRL+ high titer [≥1:8])
- HSV-2 (Presence/absence)
- Bacterial vaginosis (0-3 Normal; 4-6 Intermediate; 7-10 BV)

# 8. Analyses

## 8.1 Primary Objective 1-Feasibility

Feasibility will be examined by sex and age group (15-19 and 20-24 years) using the following outcomes:

- proportion of selected individuals who were visited (regardless of the outcome of visit).
- proportion of visited individuals who were contacted after ≥1 contact attempt

The proportion of those who were not contacted and reasons for failing to contact individuals will also be summarized.

## 8.2 Primary Objective 1-Acceptability

Acceptability of the study will be measured as the proportion of individuals who consented to participate after receiving information about the study and agreed to sample collection (e.g. blood, vaginal swabs and urine). The denominator will include individuals who were selected and contacted.

Acceptability of RTI sample collection among participants will also be measured among individuals who provided samples (swabs or urine), separately for males and females. Medians and interquartile ranges and Box-and-whisker plots will be used to summarize data on the following questions:

- Using a scale 0 to 100 (0 -easy and 100-difficult), how easy or difficult was it to:
- understand the study
- understand instruction for swab (analysis will be restricted to females)
- collect vaginal swab (analysis will be restricted to females)
- understand instruction for urine (analysis will be restricted to males)
- Using a scale 0 to 100 (0-agree and 100-disagree), Disagree or agree with statement about collection of samples:
- felt comfortable
- felt relaxed
- trusted was doing it correctly
- samples taken in a private location
- anxious
- embarrassed

## 8.3 Primary Objective 2-Prevalence of curable STIs, HSV2 and BV

The prevalence (and the 95% confidence interval) of *T. vaginalis*, HSV-2, syphilis, *N. gonorrhoeae*, *C. trachomatis* will be presented overall and separately for males and females and by age group.

Sampling weights will be applied to account for unequal probabilities of selection in the stratified sample design (335 individuals selected from each age group and sex stratum). Sampling weights will be calculated as the inverse probability of selection (i.e. number of individuals sampled in the stratum/ total individuals in the stratum); this will have the effect that participants in the under-represented strata get a larger weight and participants in the over-represented strata get less weights.

In addition, weights will be applied for non-response, calculated as the inverse probability of study participation in strata defined by age group, sex and residence location (urban/peri-urban/rural) using logistic regression. This will be done by combining the data from the entire sampled population with that from the study population, and performing a logistic regression with sex, age group & residence as predictors in the model, to get the predicted probability of participation. The inverse of this predicted probability will be used as the response weight, which will be combined with the sampling weight.

Variables:

- Any curable STIs (1-if diagnosed with at least one STI (chlamydia, gonorrhoeae, trichomoniasis, syphilis) 0-None)
- Chlamydia trachomatis (Presence/absence)
- Neisseria gonorrhoeae (Presence/absence)
- Trichomonas vaginalis (Presence/absence)
- Syphilis: negative (TP-/VDRL-); early or previously treated infection (TP+/VDRL-); active syphilis (TP+/VDRL+ low titer [<1:8]; TP+/VDRL+ high titer [≥1:8])
- HSV-2 (Presence/absence)
- Bacterial vaginosis (Presence/absence)

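### SAP section 8.3 prints the selection probability where the sampling weight should be; coded as printed, it would reverse the weighting of the prevalence estimates

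*SAP*

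**What the plan says.** SAP section 8.3 describes the sampling weight in three ways within one sentence.

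- **In words, and then as a ratio introduced by i.e.:** "Sampling weights will be calculated as the inverse probability of selection (i.e. number of individuals sampled in the stratum/ total individuals in the stratum".
- **By its effect:** "participants in the under-represented strata get a larger weight and participants in the over-represented strata get less weights".

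The design behind it is a fixed number per stratum: "335 individuals selected from each age group and sex stratum". The prevalences "will be presented overall and separately for males and females and by age group". A second weight, for non-response, is defined in the next paragraph: "The inverse of this predicted probability will be used as the response weight, which will be combined with the sampling weight".

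**The concern.** The words and the stated effect agree with each other. The ratio, taken as the weight, agrees with neither. It is also the only explicit formula given for the sampling weight, so it is what a programmer is likely to copy.

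The weighted prevalence is the estimator for primary objective 2 (section 5.1). Section 8.3 says the weights are there because selection probabilities differ. With a fixed 335 per stratum, that can only mean that the stratum totals differ. The SAP also reports prevalence by sex and age, and section 8.4.2 treats both as a priori confounders, so differing prevalences are plausible.

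A reversed weight would be hard to notice. A weighted proportion does not depend on the scale of the weights, so values below 1 run without error and return plausible figures. The reversed weight would also be multiplied by a response weight that section 8.3 inverts correctly, so the product would combine a probability with an inverse probability.

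**Working it through.** The SAP prints no numeric weight or prevalence for this point, so there is no figure to reproduce. The check is algebraic, with illustrations.

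**Inputs from the SAP.** Number selected per stratum n = 335 (section 8.3), in four age-by-sex strata, so 4 × 335 = 1,340 selected.

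**Assumed inputs.** Stratum totals N and prevalences p, because the SAP gives neither. All results are expected values with equal effective numbers per stratum (full response, or response weights that restore it).

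**Step 1: direction of the weight.**

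- Selection probability = n/N = 335/N. This is the printed ratio.
- Inverse probability = N/n = N/335.
- For N = 4,000 and 2,000, the printed ratio gives 335/4,000 = 0.084 and 335/2,000 = 0.168. The inverse gives 4,000/335 = 11.94 and 2,000/335 = 5.97.

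The larger stratum is the under-represented one. It gets the smaller weight under the printed ratio and the larger weight under the inverse.

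**Step 2: two pooled strata.** Let the sizes be in ratio r:1, with prevalence p1 in the larger and p2 in the smaller.

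- Correct = (r·p1 + p2)/(r + 1)
- Unweighted = (p1 + p2)/2
- Printed ratio as weight = (p1/r + p2)/(1/r + 1) = (p1 + r·p2)/(1 + r)

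The error from the printed ratio is (p2 − p1)(r − 1)/(r + 1), exactly twice the unweighted error. It is zero if r = 1 or p1 = p2. With p1 = 10% and p2 = 25% (assumed):

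| r | Correct | Unweighted | Printed ratio |
|---|---|---|---|
| 1.2 | (12 + 25)/2.2 = 16.8% | 17.5% | (10 + 30)/2.2 = 18.2% |
| 1.5 | (15 + 25)/2.5 = 16.0% | 17.5% | (10 + 37.5)/2.5 = 19.0% |
| 2 | (20 + 25)/3 = 15.0% | 17.5% | (10 + 50)/3 = 20.0% |

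**Step 3: four strata.** Assumed prevalences: males 15-19 5%, males 20-24 10%, females 15-19 15%, females 20-24 30%. Totals are listed in that order. Each cell shows the true value, then the value with the printed ratio as weight.

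| Assumed totals | Overall | Males | Females | 15-19 | 20-24 |
|---|---|---|---|---|---|
| 3000/3000/3000/3000 | 15.0 / 15.0% | 7.5 / 7.5% | 22.5 / 22.5% | 10.0 / 10.0% | 20.0 / 20.0% |
| 3500/2800/3300/3000 | 14.7 / 15.3% | 7.2 / 7.8% | 22.1 / 22.9% | 9.9 / 10.2% | 20.3 / 19.7% |
| 4000/2000/4000/2000 | 13.3 / 16.7% | 6.7 / 8.3% | 20.0 / 25.0% | 10.0 / 10.0% | 20.0 / 20.0% |
| 6000/2000/6000/2000 | 12.5 / 17.5% | 6.3 / 8.8% | 18.8 / 26.3% | 10.0 / 10.0% | 20.0 / 20.0% |

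The unweighted overall figure is 15.0% throughout. With N/n as the weight, every estimate equals the true value. With totals 4000/2000/4000/2000 and 10% prevalence in every stratum, the printed ratio also returns 10.0%, so unequal size alone causes no bias.

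**Step 4: is the printed ratio always worse than no weights?** For two pooled strata with equal effective numbers, yes (step 2). For the four-stratum overall estimate, not always. Take totals 2000/3000/3000/5000 with prevalences 20/10/10/20%:

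- True = (400 + 300 + 300 + 1,000)/13,000 = 15.38%
- Unweighted = 15.00%
- Printed ratio = (15×20 + 10×10 + 10×10 + 6×20)/41 = 15.12%, with relative weights 15, 10, 10 and 6

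**The case against.** The strongest reply is that the SAP does not prescribe reversed weights. The parenthesis directly follows the words for selection probability and is exactly that probability. If it explains only those words, the weight is the inverse of the ratio and nothing is wrong. The stated effect supports this reading, as does the response weight, which is correctly described as an inverse. This stands as evidence of intent: the authors almost certainly mean N/n. It does not make the sentence safe to program, because a formula introduced by i.e. after the name of the weight is ordinarily read as defining that weight.

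The reply is also right about consequences. A reader might infer that the prevalences are biased, or that every overall, by-sex and by-age figure is wrong. The SAP does not support this. Bias needs literal coding and pooled strata that differ in both size and prevalence. By-age figures escape if the sexes are equally numerous within an age group. Bacterial vaginosis is measured in young women only (section 5.1), so its by-age figures each rest on a single stratum. If the by-sex and by-age presentation means sex-by-age cells, those are unaffected too. Nor is the printed ratio always worse than no weighting, as step 4 shows.

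Finally, the bias could be small. With mildly unequal totals, the illustration gives 15.3% against 14.7% overall, a 0.6-point difference. With 447 participants (section 4), a simple 95% interval at 15% is about ±3.3 points (1.96 × √(0.15 × 0.85/447)). That limits the likely size; it does not remove the contradiction.

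**Conclusion.** The point holds as an internal contradiction in one sentence of section 8.3: the printed ratio is the selection probability and, read as the weight, conflicts with both the name and the stated effect of the weight. The correct rule can be recovered from that same sentence, so this is a wrong or ambiguous formula, not evidence that any estimate has been computed wrongly.

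The consequence is conditional. If the ratio were coded as printed, the weighting would be reversed, and pooled prevalences would be exposed to bias where the strata differ in both size and prevalence. The assumed scenarios range from no error to 5 points, and to 7.5 points for females when the younger stratum is three times the older. These figures rest on assumed totals and prevalences and on equal effective numbers per stratum; the actual size cannot be determined from the SAP. Because the formula feeds the estimator of a primary objective and costs almost nothing to correct, it should be corrected.

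**What to change.** Replace the parenthesis in section 8.3 with an explicit formula: sampling weight = total individuals in the age-sex stratum / number selected in the stratum (N/335). The rest of the sentence can stay, since it describes this weight correctly.

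Add a programming check: within each stratum, the sampling weights summed over all 335 selected individuals (not only the participants, and before the response weight is applied) must equal the stratum total. With N/335 the sum is 335 × N/335 = N; with the printed ratio it would be 335²/N, so the slip would normally show at once. If code already exists, confirm that it uses N/n.

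The cost is one line of SAP text and one line of code, plus the check. No new data are needed.

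### One participation-based response weight serves every infection, so pooled prevalences can shift if specimen completion and prevalence both vary across the same sex, age or residence cells

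*SAP*

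**What the plan says.** SAP section 8.3 corrects for non-response with a weight "calculated as the inverse probability of study participation in strata defined by age group, sex and residence location". It is obtained by "performing a logistic regression with sex, age group & residence as predictors in the model". The section continues: "The inverse of this predicted probability will be used as the response weight, which will be combined with the sampling weight". One model and one weight are described, and no infection is treated differently. Participation is not formally defined. Section 4 describes the study group thus: "447 young men and women agreed to participate and provided informed consent".

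Section 7.2 lists agreement to participate as one acceptability outcome and, as another, "proportions who agreed to each sample collection (e.g. blood, vaginal swabs and urine". Section 8.2 then says that acceptability of sample collection "will also be measured among individuals who provided samples (swabs or urine", that is, in a subset defined by having given a specimen. Section 8.3 states no denominator or weight for a participant who has no result for a given infection.

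**The concern.** The response weight is meant to restore the population mix by sex, age group and residence. It does so for the group whose probability was modelled, which is the participants. The group analysed for a given infection is those participants with a result for it, and the plan's own acceptability outcomes allow this group to be smaller. Where the two groups differ unevenly across cells, the weights no longer add up to the population, and the mix is only partly restored.

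The estimates at stake are the pooled prevalences under Primary Objective 2. The set of people with results may also differ by specimen. Syphilis is classified from TP and VDRL results, which presumably need blood, while section 8.2 asks women about swabs and men about urine. Prevalences of different infections could then be standardised to slightly different mixes.

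**Working it through.** The SAP gives no figure on this point to reproduce, so the check is algebra plus assumed scenarios.

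**Inputs from the SAP.** Section 8.3 has "335 individuals selected from each age group and sex stratum", which gives 4 × 335 = 1,340 selected. Section 4 has 447 participants, so participation is 447/1,340 = 33.4%.

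**Inputs assumed.** Stratum population sizes (taken as equal), prevalences and specimen completion are not in the SAP.

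**Weight total per stratum.** Let N be the stratum population, r the participation probability (assumed to be reproduced by the model) and c the share of participants with a result.
- Sampling weight: N/335. Response weight: 1/r. People with a result: 335·r·c.
- Weight total as planned: (N/335)·(1/r)·(335·r·c) = N·c. Participation cancels; completion does not.
- With a response weight of 1/(r·c), the total is N.

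The expected pooled prevalence as planned is therefore Σ(N·c·p)/Σ(N·c), against a population value of Σ(N·p)/Σ(N).

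**Two strata, women 30% and men 10%, population value 20.0%.**
- Completion 98% women, 90% men: (0.294 + 0.090)/1.88 = 20.4%, a shift of +0.4 points.
- 95% and 80%: (0.285 + 0.080)/1.75 = 20.9%, +0.9 points.
- 98% and 70%: (0.294 + 0.070)/1.68 = 21.7%, +1.7 points.

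**Four strata (men 15–19, men 20–24, women 15–19, women 20–24).** Overall prevalence as planned:

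| Completion | Prevalences 3/7/10/14%, population value 8.50% | Prevalences 5/15/20/45%, population value 21.25% |
|---|---|---|
| Equal everywhere (100% or 80%) | 8.50% (0) | 21.25% (0) |
| Men 95%, women 85% | 8.31% (−0.19) | 20.62% (−0.63) |
| Men 95%, women 70% | 7.97% (−0.53) | 19.55% (−1.70) |
| Men 70%, women 95% | 9.03% (+0.53) | 22.95% (+1.70) |
| Ages 15–19 70%, ages 20–24 90% | 8.75% (+0.25) | 22.34% (+1.09) |

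Weights of 1/(r·c) return the population value in every row, provided results are missing at random within strata.

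**Which totals move.** When completion differs only by sex, the male and female totals do not change. When it differs by age (last row, second set of prevalences), the female total is (0.7 × 20 + 0.9 × 45)/1.6 = 34.1% against 32.5%, and the male total is (0.7 × 5 + 0.9 × 15)/1.6 = 10.6% against 10.0%.

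**Scale.** Under simple random sampling with n = 447, the standard error at 21.25% is √(0.2125 × 0.7875/447) = 1.9 points, so the largest overall shift is 1.70/1.93 = 0.88 of a standard error. The 95% half-widths are about 3.8 points at 21.25% and 2.6 points at 8.5%. Losing untested people raises the standard error: if participants split equally by sex, 98%/70% completion leaves 447 × 0.84 = 375 people, the standard error at 20% is 2.06 points, and the ratio is 1.67/2.06 = 0.81. An age-group estimate can move by more points. With men at 70% and women at 95%, ages 20–24 give (0.7 × 15 + 0.95 × 45)/1.65 = 32.3% against 30.0%. It also rests on about half the people: 447/2 × 0.825 = 184, with a standard error of √(0.3 × 0.7/184) = 3.4 points.

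**The case against.** The strongest reply is that the effect may not exist. Planning to measure specimen uptake does not show that refusal is material, and participation is undefined. The first sentence of section 8.2 joins consent with agreement to sample collection, so participation could be read to include giving samples. The gap would then shrink to invalid results and differences between specimen types. This stands as a limit on size. It does not remove the mismatch, because one weight cannot fit different result sets for blood and for swab or urine if those sets differ.

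A reader might infer that the planned prevalences are biased, or biased in a known direction. The SAP does not support this. A shift needs completion and prevalence both to vary across the same cells, no rate for either is given, and the assumed scenarios go both ways. Nor can it be inferred that the male and female totals are affected as a matter of course. Bacterial vaginosis is a women-only outcome, so a difference between the sexes cannot touch it.

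It is also fair that this is a secondary layer. About two thirds of those selected (893 of 1,340) did not take part, and section 8.3 already weights for that. Every overall shift above is smaller than the matching 95% half-width.

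**Conclusion.** The point holds as a conditional mismatch. Section 8.3 models participation, whereas the estimate is made among people with a result, and the plan itself treats these as separable. If completion differs by sex, age group or residence and prevalence differs across the same cells, the overall and age-group prevalences shift toward cells with higher completion. The male and female totals do so only if completion differs by age or residence.

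Direction and size cannot be determined from the SAP. The assumed scenarios put the shift in overall prevalence at about 0.2 to 1.7 points either way, below one standard error, and at zero when completion is uniform. These figures rest on equal stratum populations, assumed prevalences and completion rates, and a simple-random-sampling standard error. The change is worth making because it is cheap, matches the weight to the group analysed, and alters almost nothing if completion proves even.

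**What to change.** In section 8.3:
- Define the response event as having a valid result for the test in question (1 = yes, 0 = otherwise) among all sampled individuals.
- Fit the same logistic model, with the same predictors, once per specimen type (blood; swab or urine), and use the matching weight for each infection.
- For the any-curable-STI composite, use people with all component results, with a weight modelled on that event.
- Report the number tested beside each prevalence.

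The cost is a change of wording and two or three runs of a model already planned, giving two or three weight sets in place of one, with slightly more variable weights. The composite would exclude people with partial results, including some already known to be positive on one component, and the SAP should say so. The correction is valid only if results are missing at random within sex, age and residence cells; it does not address refusal related to infection status inside a cell.

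### The response model in SAP section 8.3 keeps sampled people who have left the surveillance area in its denominator, so weighted prevalence can be biased for residents if out-migration differs between weighting cells

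*SAP*

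**What the plan says.** Section 8.3 of the SAP describes two weights for the prevalence estimates. The sampling weight is the inverse of the selection probability, with "335 individuals selected from each age group and sex stratum". The response weight comes from "combining the data from the entire sampled population with that from the study population" and then "performing a logistic regression with sex, age group & residence as predictors in the model, to get the predicted probability of participation". On its use, the section says: "The inverse of this predicted probability will be used as the response weight, which will be combined with the sampling weight". It gives no rule for a selected person who turns out to be ineligible.

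Section 3 defines the study population as "Young men and women aged 15-24 years living in the Africa Centre DSA" and lists "resident at the time of the study" among the eligibility criteria. Age, by contrast, is tested when the sample is drawn. Section 7.1 adds: "Reasons for non-contact (e.g. migration) among sampled individuals will also be presented". Section 8.1 also commits to summarising why individuals could not be contacted. Section 4 reports that "447 young men and women agreed to participate and provided informed consent".

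**The concern.** Someone who was selected but has left the surveillance area before the visit fails the residence criterion. That person is not a non-respondent, because nobody in the target population is missing on their account. A response model fitted to everyone selected cannot tell the two apart: its predictors carry no information on eligibility, and both groups enter as people who did not take part. Residents who did take part in a high-migration cell are then weighted up to stand in for people who no longer live there.

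The weighted prevalence is a primary objective, and response weights carry much of the load here. With 4 x 335 = 1340 selected and 447 participants, 893 selected people did not take part and the average response weight is about 1340/447 = 3.0. Who belongs among those 893 as a true non-respondent therefore affects the weights directly.

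**Working it through.** The SAP states no response rate, out-migration rate or precision figure for this analysis, so there is no figure of its own to reproduce.

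**Inputs.** From the SAP: 335 selected per stratum, four age-by-sex strata, 447 participants. Assumed, because the SAP gives no values: out-migrated share m per cell, prevalence per cell, equal frame sizes. The sampling weight is taken as N/n, the inverse of the selection probability.

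**Step 1: weight in one cell.** Let N be the frame count, n the number selected, r the participants and m the share who have left.
- As planned: (N/n) x (n/r) = N/r. Participants are scaled up to the whole frame.
- For residents: (N/n) x (n(1-m)/r) = N(1-m)/r.
- Ratio: 1/(1-m). For m = 10%, 20%, 30% and 40% this is 1.11, 1.25, 1.43 and 1.67.

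The ratio is exact if the model reproduces each cell's participation rate, and approximate for a main-effects logistic model.

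**Step 2: relative weight of two cells.** Only relative weights affect a prevalence. A high-migration cell is over-weighted against a low-migration cell by (1-m_low)/(1-m_high).
- 5% v 30%: 0.95/0.70 = 1.36.
- 5% v 15%: 0.95/0.85 = 1.12.
- Equal shares: 1, so no effect.

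**Step 3: effect on prevalence.** Two age groups within one sex, equal frame sizes, assumed prevalence 5% (younger) and 12% (older).
- As planned, whatever the out-migration: (5% + 12%)/2 = 8.5%.
- Residents, 5% v 30% out-migration: (0.95 x 0.05 + 0.70 x 0.12)/(0.95 + 0.70) = 0.1315/1.65 = 8.0%. Difference about 0.5 points.
- Residents, 5% v 15% out-migration: (0.95 x 0.05 + 0.85 x 0.12)/(0.95 + 0.85) = 0.1495/1.80 = 8.3%. Difference about 0.2 points.

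A wider range of assumptions, same formula:

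| Out-migration, younger v older | Prevalence | As planned | Residents | Difference (points) |
|---|---|---|---|---|
| 20% v 20% | 10% v 20% | 15.0% | 15.0% | 0 |
| 5% v 15% | 10% v 20% | 15.0% | 14.7% | 0.3 |
| 10% v 30% | 10% v 20% | 15.0% | 14.4% | 0.6 |
| 10% v 40% | 10% v 20% | 15.0% | 14.0% | 1.0 |
| 10% v 40% | 5% v 25% | 15.0% | 13.0% | 2.0 |

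**Step 4: check with the planned model.** A logistic regression with sex, age group and a three-level residence location was fitted to expected counts in 12 cells (1340 selected, 447 participants). Out-migration was set at 10% v 30% by age group, so eligible people number 1340 x 0.80 = 1072 and response among residents is 447/1072 = 41.7% in every cell. With everyone selected in the denominator, predicted participation was 37.5% in the younger group (0.417 x 0.90) and 29.2% in the older (0.417 x 0.70). The model therefore adjusts for a response difference that does not exist. Weighted prevalence was 15.0%, against 14.4% when the model was restricted to eligible people.

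**The case against.** **The rule is inferred.** No sentence says that people who have left are coded as non-responders. That is true, but the SAP does state the denominator, and it is everyone selected. With no exclusion, someone who has left can enter only as a non-participant. An unseen sampling section would not alter that denominator, so this is not a detail left to the protocol.

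**Migration may not mean leaving.** The word appears once as an example, without rate, direction or definition. It may cover moves within the surveillance area, and those people may remain eligible and be genuine non-respondents. This stands, and it is why the rule needs a definition.

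**The effect is small.** If about half of the 447 participants are men (an assumption), the 95% interval around 8% is roughly 1.96 x sqrt(0.08 x 0.92/223.5) = 3.6 points either side before any design effect. A shift of 0.2 to 0.5 points is small beside that. This also stands, though the interval does not reflect a systematic shift.

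**The remedy has its own difficulty.** Section 8.1 distinguishes visited from contacted individuals, and eligibility is unknown for many who were not reached. Dropping known leavers while keeping everyone of unknown status can distort the weights if visit outcomes were recorded more fully in some strata. Hence unknown eligibility needs a rule in the main analysis, not only in a sensitivity analysis.

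**Two stronger readings are tempting and not supported.** A reader might infer that the frame was out of date. The SAP draws it from a 14-week surveillance round (section 1) and gives no interval between frame and visit. A reader might also infer that overall and by-sex estimates are biased as a matter of course. They are biased only under the conditions given in the verdict.

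**Conclusion.** The concern holds in a conditional form. As written, section 8.3 scales participants up to the full frame, while section 3 defines the target as residents. Each weighting cell is inflated by about 1/(1-m).

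- Overall prevalence is biased for residents if out-migration and prevalence both differ across weighting cells.
- A by-sex or by-age-group estimate is biased only if both differ within that sex or age group. Within a single age-by-sex stratum, that can happen only through residence location.
- Uniform out-migration has no effect.

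The size cannot be determined from the SAP. Under the assumed values above, the shift runs from zero to about 1 point in moderate settings, and reaches 2 points only with strong contrasts in both out-migration and prevalence. The point deserves correction because it concerns the stated denominator of a primary estimate and is cheap to put right, not because a large error has been shown.

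**What to change.** Amend section 8.3 to:

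1. Fit the response model among selected people not known to be ineligible. Exclude those whose recorded visit outcome shows that they had left the surveillance area or died. Keep people who moved within the area as eligible.
2. State a rule for people never visited or never located. One option is to apply the cell's known-eligibility rate: e = known eligible/(known eligible + known ineligible), with each person of unknown status counted in the response denominator with weight e.
3. Report the estimate with everyone selected in the denominator as a sensitivity analysis.
4. Tabulate, by sex, age group and residence location, the numbers known eligible, known ineligible and of unknown status, so that readers can see whether out-migration differs across cells.

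The cost is SAP wording and a modest amount of programming. The reasons for non-contact that sections 7.1 and 8.1 already commit to reporting should supply the data. The downside is that the result depends on how completely visit outcomes were recorded across strata; the sensitivity analysis and the table make that dependence visible.
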